## Abstract

**Background:**

Many people living with HIV suffer from depressive symptoms. In a previous pilot study, self-help cognitive behavioral therapy (in booklet format) was found to be effective in treating depressive symptoms in people with HIV. We developed an online self-help program in Dutch and English (based on the booklet) for people with HIV and depressive symptoms. Besides the main question regarding the effectiveness of the program aimed at lowering depressive symptoms, sub-questions will focus on the moderators of treatment success (for which patients is the program especially beneficial?) and the mechanisms of change underlying the treatment outcome (which mediators affect the outcome of treatment?). In this paper, the protocol of the study will be described.

**Methods/design:**

The effectiveness of the program will be investigated by comparing the intervention group with a waiting list-control group in a randomized controlled design, by including a pretest and three post-tests. The self-help program contains four main components: activation, relaxation, changing maladaptive cognitions, and goal attainment. Participants with mild to moderate depressive symptoms will work on the program for 6 to 10 weeks, during which a coach will provide motivational support by telephone once a week. Participants in the control condition will receive weekly minimal support from a coach for 8 weeks, and after the second post-test, they can gain access to the self-help program. Depressive symptoms and possible mediators (e.g., activation, cognitive coping, self-efficacy, and goal adjustment) will be assessed by self-report three times during the intervention/waiting period and at the pretest and first post-test.

**Discussion:**

The proposed study aims to evaluate the effectiveness of an online self-help intervention for people with HIV and depressive symptoms. If the intervention is shown to be effective, the program will be implemented. Consequently, many patients with HIV could be reached, and their psychological care may be improved.

**Trial registration:**

Netherlands Trial Register: NTR5407

**Electronic supplementary material:**

The online version of this article (doi:10.1186/s13063-016-1292-6) contains supplementary material, which is available to authorized users.

## Background

Currently, HIV is a chronic disease that requires the use of medication. Along with the physical problems that people living with HIV (PLH) may experience (e.g., linked to the side effects of medication or comorbidities), psychological symptoms are also prevalent [1, 2]. Specifically, depressive symptoms are often reported by PLH. Many PLH struggle, for example, with the daily use of medication and thinking about whom to tell about their HIV [3]. This and more general life stressors may lead to depressive symptoms in PLH. In turn, PLH with depressive symptoms have a higher chance of nonadherence to their medication [4]. This can result in more physical symptoms and illness. Therefore, the treatment of depressive symptoms in PLH is important.

Various treatments are available for PLH with depressive symptoms. Group and individual therapies exist, and many of these contain cognitive behavioral components (see review studies [5–9]). These treatments are effective in decreasing depressive symptoms and improving the quality of life in PLH [2, 5, 7–9]. Furthermore, beneficial effects were also found for medication adherence [6].

These group and individual therapies have some disadvantages. First, patients and therapists should meet in person during office hours for the treatment. Second, the costs of these treatments are high. Third, for HIV-specific programs, the stigma is a significant barrier to service delivery and utilization [10]. A self-help program could be a way to overcome these disadvantages and barriers. The evidence base for low-intensity interventions has been growing in recent years, with high-quality trials supporting the effectiveness of self-help cognitive behavioral therapy (CBT) for depression [11–13].

A low-cost CBT self-help booklet for PLH was developed based on prior research and a needs assessment [14–17]. The self-help booklet contains three main components: relaxation, changing maladaptive cognitions, and goal attainment. The effectiveness of this booklet was tested in a pilot randomized controlled trial (RCT) [18]. The results indicated that this intervention was effective in reducing the depressive symptoms in PLH, compared to waiting list controls. However, in this RCT, 25 % of the participants dropped out during the intervention phase. Elements should therefore be added to retain more PLH in the program and to increase the effectiveness. In addition, several participants indicated they were worried that having the booklet in their home would disclose their HIV-positive status. They would have valued a less stigmatizing mode.

Therefore, the self-help booklet was converted into an Internet version. The online program contains eight lessons, which can be completed in 6 to 10 weeks. An online program has a lower stigma, is easily accessible, can reach more people, and has lower long-term costs. Previous studies showed that online self-help therapy for depression in people with chronic illness was effective [19]. In addition to being converted from a booklet into an Internet version, the program was expanded in three ways in the proposed study:An activation component was added, in which participants will be stimulated to perform (small) activities (e.g., wake up on time). Activation is often used in CBT for depression as a first step [20].Minimal coaching with motivational interviewing will be offered. A meta-analysis [12] showed a greater effectiveness of the Internet therapy when coaching was included, also when given in a minimal format. In addition, our recent studies including minimal coaching showed attrition rates between 10 and 15 % [21].Finally, in the current study, the online intervention will be available in Dutch and English to reach more PLH in the Netherlands (and possibly in other countries in the future).

In 2014, the development of the online program was finalized, and we asked a focus group (four volunteers from the Dutch HIV Association) to evaluate the program. Thereafter, we adapted the program, and we conducted a pilot study with 20 PLH with depressive symptoms (14 males; mean age = 48.65 years, *SD* = 10.86) to test the feasibility of the program. Participants were approached via advertisements on the website and in the magazine of the Dutch HIV Association and were representative of the Dutch HIV population. The results of the pilot study showed that the program was effective in this small group; depressive symptoms decreased from pre-test to post-test. Furthermore, participants thought the program was easy to use and helpful to them. These results encouraged us to execute a large study on the effectiveness of the online self-help program.

The aim of the present paper is to describe the study protocol. The proposed study is a randomized controlled trial; the online self-help program will be compared with a waiting list control condition. The study will include a pretest and three post-tests for the intervention condition (directly after the intervention and 3 and 6 months afterward) and a pretest and two post-tests (directly after the 8-week waiting period and 3 months afterward) for the control condition. After the second post-test (5 months after the pretest), the participants in the control group can also begin the program. Concluding, we will investigate the effectiveness of the online self-help program in decreasing depressive symptoms in the short and long term. In addition, the moderators (for which patients is the program especially beneficial?) and mediators (which mechanisms affect the outcome of treatment?) will be assessed.

## Methods/design

### Design

The study is a randomized controlled trial; participants will be randomly allocated to the intervention or the control group. Stratified randomization by treatment center and sex will be conducted. Stratification by sex is conducted, as there will be more male participants in the study, and the allocation of approximately the same number of females to the intervention group as to the control group is preferred. In addition, stratification by treatment center is being conducted because the number of (included) patients will differ among the treatment centers. Approximately equal allocation to each of the groups also in the small treatment centers, is important. This will be realized by creating random number tables for each treatment center, divided by sex. Randomization will take place in blocks of 12 participants for each treatment center. Males and females will represent separate blocks, with six males and six females for each treatment center, of which half will be randomly allocated to the intervention group, and half will be allocated to the control group. Participants, coaches, and researchers cannot be blind for allocation to conditions. Participants will be allocated to one of the conditions after the pretest. The random number tables will be created by an independent researcher, and the allocation sequence will be concealed from the main researcher, who enrolls and informs participants.

The design consists of multiple measurements, one pretest, three post-tests (two in the control group), and three assessments during the intervention/waiting period. Figure 1 shows a flow chart of the study design, and the SPIRIT Checklist is presented in Additional file 1. The study is approved by the medical ethics committee of the Leiden University Medical Center (LUMC; nr. P14.091). Online informed consent will be obtained from all participants.

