### Participants

At least 200 participants who are PLH with mild to moderate depressive symptoms will be included. Participants will be approached in 23 of the 27 HIV treatment centers throughout the Netherlands during their regular visits to the HIV nursing consultants and doctors. To be eligible to participate in the study, a participant must meet all of the following criteria: being HIV positive, exhibiting mild to moderate depressive symptoms (defined as Patient Health Questionnaire 9 (PHQ-9) [22] score > 4 and < 20), age 18 and older, having sufficient knowledge of the Dutch or English language, able to access the Internet, having an e-mail address, and available for the next 8 weeks to work on the intervention.

An eligible participant who meets any of the following criteria will be excluded from participation in the study: being in the first half year following HIV diagnosis, having severe cognitive impairments (e.g., forgetfulness), exhibiting severe depressive symptoms (defined as PHQ-9 score of 20 or higher), experiencing suicidal ideation (indicated by a score > 1 on the suicide item of the PHQ-9), showing an absence of depressive symptoms (indicated by a PHQ-9 score of 4 or lower), undergoing treatment presently by a psychologist or psychiatrist, or on antidepressants for less than 3 months or has experienced a change of type or dose of antidepressants in the past 3 months. In case of severe depressive symptoms (using the set criterion) and/or suicide ideation, patients will be referred to their general practitioner or the HIV treatment center.

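### Fixed blocks of six in 46 sparse centre-by-sex strata weaken, but do not remove, the intended balance, and make about 13–17% of allocations deducible to an enroller who knows the block size and tracks the lists

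*Protocol article*

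**What the plan says.** The Design section of the protocol article states: "Stratified randomization by treatment center and sex will be conducted". It gives two reasons. Women will be the minority, and similar numbers of them are wanted in each arm. Centres will recruit different numbers, and roughly even allocation is called important in the small ones too.

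The means are "creating random number tables for each treatment center, divided by sex". The block size is fixed: "Randomization will take place in blocks of 12 participants for each treatment center". This is then split by sex: "Males and females will represent separate blocks, with six males and six females for each treatment center". Assignment within each of these is even between the arms. Each centre-by-sex list therefore runs in blocks of six, three per arm.

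On the number of centres, the Participants section says: "Participants will be approached in 23 of the 27 HIV treatment centers". The target is at least 200 participants.

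On concealment, an independent researcher creates the tables, and "the allocation sequence will be concealed from the main researcher, who enrolls and informs participants". Allocation follows the pretest. The same section says that participants, coaches and researchers cannot be blind to condition.

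**The concern.** Permuted blocks control balance only as far as blocks are filled. With many strata and few participants in each, most lists stop part-way through a block, and the leftover imbalances add up across centres. This affects women most, because their lists are the sparsest. Balance by sex is one of the two stated aims, and the Sample size section names group by sex as an interaction that the trial should be able to detect.

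Busier lists carry a different risk. When the block size is constant and past assignments are known, the last places in a block can be worked out without seeing the list. The person who enrols is unblinded, some entry criteria call for judgement (language, availability, cognitive impairment), and the outcomes are self-reported. Foreknowledge of an allocation could then influence who is entered.

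**Working it through.** **Inputs.** From the document: 23 centres, two sexes, blocks of six split 3:3, at least 200 participants. The only sex mix given is that of the pilot (14 men among 20 participants, so 30% women). Assumed, because the document gives neither centre sizes nor the trial's sex mix: 15–30% women, and centres either equal or very unequal in size. The plan states no figure for expected balance or predictability, so there is none to reproduce.

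**1. Sparseness.**
- Strata: 23 × 2 = 46.
- First-block places: 46 × 6 = 276, against 200 participants.
- Mean per stratum: 200/46 = 4.3, less than one block.
- Completed blocks: at most 200/6 = 33.

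In simulation (10–30% women), 28–34 of the 46 strata never complete a first block, and 57–73% of opened blocks end unfilled.

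**2. Balance within one list (exact).** If *k* of six places are used, the variance of the arm difference is *k*(6 − *k*)/5. With simple randomisation it is *k*.

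| *k* | 1 | 2 | 3 | 4 | 5 | 6 |
|---|---|---|---|---|---|---|
| Block of six | 1.0 | 1.6 | 1.8 | 1.6 | 1.0 | 0 |
| Simple | 1 | 2 | 3 | 4 | 5 | 6 |

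Blocking does nothing for a list with one participant and little for two: they fall in the same arm with probability 2/5, against 1/2. From three upwards the gain is clear.

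Only the last block of a list contributes, so there is a ceiling whatever the centre sizes:
- Women: SD at most √(23 × 1.8) = 6.4.
- Whole trial: SD at most √(46 × 1.8) = 9.1.
- Simple randomisation: √30 = 5.5 for 30 women, √60 = 7.7 for 60 women, √200 = 14.1 for the whole trial.

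**3. Balance over the trial (simulation, N = 200).**

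| | As planned | Simple | Minimisation on sex and centre |
|---|---|---|---|
| SD of difference in women | 3.9–5.5 | 5.1–7.9 | 1.4–1.5 |
| SD of overall difference | about 6–8 | about 14 | smaller than planned |

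At the pilot's 30% women (about 60), the mean absolute difference under the plan is 3.6–4.2, roughly 32 v 28. At 10% women the plan barely helps: 3.0–3.2 against 3.4–3.6 with simple randomisation. In centres with six or fewer participants, the mean difference is 0.9–1.2 as planned and 1.4–1.8 with simple randomisation.

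**4. Predictability.** Of the 20 possible 3:3 sequences, the 4th place is certain in 2 (0.1), the 5th in 8 (0.4) and the 6th in all (1.0). A filled block therefore has 0.1 + 0.4 + 1.0 = 1.5 certain places of six, or 25%. Many blocks never reach those places, so over the whole trial 13–17% of allocations are certain. The best guess is right 63–65% of the time, against 50% with simple randomisation. Both figures assume that the enroller knows the block size and tracks past assignments by centre and sex.

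**The case against.** A reader might infer that the stated balance is not delivered. The documents do not support that. The Design section asks only for approximately equal numbers, and 32 v 28 women is approximately equal. The plan also beats simple randomisation in small centres and overall. Nor is the cost to the analysis large. The Statistical analyses section already names sex as an example covariate and explores a centre effect, and a 34 v 26 split of 60 women keeps 4 × 34 × 26/60² = 98.2% of the efficiency of an even split. This stands, and it limits the point to weakened balance.

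A reader might also infer that allocations were in fact foreseen. Nothing shows this. The sequence is concealed, and allocation follows the telephone screen, consent and the online pretest, so an enroller would have to predict several steps ahead while tracking up to 46 lists. The article does not say who held the lists or whether the block size was disclosed, and a condensed article may leave that out. The risk is therefore conditional. It does not vanish: hiding the list does not hide a place that follows from a fixed block size and known past assignments.

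The two weaknesses partly offset each other, since unfilled blocks never reach their certain places. The 13–17% already allows for this.

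**Conclusion.** The point holds as a moderate design weakness. Fixed blocks of six in 46 strata averaging 4.3 participants will probably leave most blocks unfilled. They give an SD of about 4 to 5.5 for the difference in women, between simple randomisation (about 5 to 8) and what minimisation achieves (about 1.5). About 13–17% of allocations could be deduced with certainty by an unblinded enroller who knew the block size and kept track.

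The counts of strata and places come straight from the document. The other figures rest on assumed centre sizes, 15–30% women for the balance SDs, 10–30% for the deducible share, and N = 200. Whether the enrolling researcher knew the block size is not stated, so neither actual foreknowledge nor selection bias can be concluded.

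**What to change.** For the design, have the independent researcher run central minimisation on sex and centre with a random element. This keeps small-centre balance, improves balance by sex and overall, and leaves no allocation certain. As a minimum, keep the present strata, vary the block sizes at random and withhold them from the enrolling researcher. Simply shortening a fixed block is not a remedy: with 20% women and unequal centres, the share of certain allocations rises from 16% with blocks of six to 26% with blocks of four and 45% with blocks of two.

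Do not stratify by sex alone. That balances women well but gives up the small-centre balance that the Design section calls important: the mean difference in small centres becomes 1.5–1.75, against 0.9–1.15 as planned.

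The cost is a short script kept by the independent researcher, with no extra participants or visits. One downside is that minimisation has a higher theoretical best-guess rate, about 73% against 64%, for someone tracking all the margins. The gain is in balance and in removing certain allocations, not in a lower guess rate.

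The Trial status section says recruitment is complete, so the scheme cannot now be changed for this trial. The report should give allocation by sex and by centre, and state whether the enrolling researcher knew the block size.

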**Fig. 1 Fig1:**
[figure not shown]
Flow chart of study design

### Participants

At least 200 participants who are PLH with mild to moderate depressive symptoms will be included. Participants will be approached in 23 of the 27 HIV treatment centers throughout the Netherlands during their regular visits to the HIV nursing consultants and doctors. To be eligible to participate in the study, a participant must meet all of the following criteria: being HIV positive, exhibiting mild to moderate depressive symptoms (defined as Patient Health Questionnaire 9 (PHQ-9) [22] score > 4 and < 20), age 18 and older, having sufficient knowledge of the Dutch or English language, able to access the Internet, having an e-mail address, and available for the next 8 weeks to work on the intervention.

An eligible participant who meets any of the following criteria will be excluded from participation in the study: being in the first half year following HIV diagnosis, having severe cognitive impairments (e.g., forgetfulness), exhibiting severe depressive symptoms (defined as PHQ-9 score of 20 or higher), experiencing suicidal ideation (indicated by a score > 1 on the suicide item of the PHQ-9), showing an absence of depressive symptoms (indicated by a PHQ-9 score of 4 or lower), undergoing treatment presently by a psychologist or psychiatrist, or on antidepressants for less than 3 months or has experienced a change of type or dose of antidepressants in the past 3 months. In case of severe depressive symptoms (using the set criterion) and/or suicide ideation, patients will be referred to their general practitioner or the HIV treatment center.

### Sample size

A power analysis was performed (with the program Power Analysis and Sample Size Software: PASS; [23]) to determine the sample size needed to assess the long-term effect of the intervention on the primary outcome depressive symptoms. Based on a medium effect size of 0.50, which proved to be realistic according to the previous pilot RCT, and assuming an alpha of .05 and a power of .80, both groups should consist of 64 participants who complete the four measurements. This sample size is also large enough to detect moderate pre-defined two-way cross-product interactions, such as the interactions of group by sex. Taking into account a dropout rate of 15 % during working on the self-help program (based on our recent studies, which included coaching [21]), at least 150 patients should be allocated to the two groups at baseline (*n* = 75 in each group). We will aim for at least 200 participants because dropout will also occur during the follow-up.

### Procedure

HIV nursing consultants and doctors in the treatment centers will screen as many PLH as possible for the level of depression at regular check-ups by means of the PHQ-2 [24]. In some of the treatment centers, the Hospital Anxiety and Depression Scale (HADS [25]) will be used instead of the PHQ-2 because this scale was already in use in these centers. HIV treatment centers will receive information about the study and a guideline for the screening. A form will be used for the screening, and the forms will be sent to the researchers. Patients will be screened over approximately 6 months; most patients visit the HIV treatment center once every 6 months. If the PHQ-2 score is > 0, patients may be referred to the researchers. Patients will receive written information about the study and permission will be asked to provide the researchers with their e-mail addresses and telephone numbers, so the researchers may contact the patients. The researchers will provide additional information to the patients and screen them more extensively with the PHQ-9. If the depression score is mild (PHQ-9 > 4) to moderate (PHQ-9 < 20), patients are eligible for the study and will be invited to participate. After giving online informed consent, participants will be asked for permission to inform their general practitioner and the HIV treatment center about participation in the study. Thereafter, all participants will complete the pretest via online questionnaires (T0). Next, participants will be randomly allocated to either the intervention or the control condition. At the start of the intervention, the personal coach will contact the participant by telephone in order to check and improve motivation by using the technique of motivational interviewing.

Subsequently, participants in the intervention group will follow the self-help program for 6 to 10 weeks and receive support from a coach (see study conditions). They will be asked to fill out online questionnaires three times during the intervention, after they complete the program (T1, a maximum of 10 weeks after T0), 3 months later (T2), and again 3 months later (T3). Participants who are allocated to the control condition will receive minimal support for 8 weeks (for details see study conditions). They will also be asked to fill out the questionnaires, including the T2. After the T2 (which is completed approximately 5 months after T0), the participants will also receive the online intervention. Coaches will monitor the well-being of participants in both groups (see ethical precautions). We will raffle off gift cards and iPods among the participants who completed all questionnaires during the study.

